## Abstract

**Background:**

Subacromial impingement syndrome (SIS) is the most frequently recorded shoulder disorder. When conservative treatment of SIS fails, a subacromial decompression is warranted. However, the best moment of referral for surgery is not well defined. Both early and late referrals have disadvantages – unnecessary operations and smaller improvements in shoulder function, respectively. This paper describes the design of a new interdisciplinary treatment strategy for SIS (TRANSIT), which comprises rules to treat SIS in primary care and a well-defined moment of referral for surgery.

**Methods/Design:**

The effectiveness of an arthroscopic subacromial decompression versus usual medical care will be evaluated in a randomized controlled trial (RCT). Patients are eligible for inclusion when experiencing a recurrence of SIS within one year after a first episode of SIS which was successfully treated with a subacromial corticosteroid injection. After inclusion they will receive injection treatment again by their general practitioner. When, after this treatment, there is a second recurrence within a year post-injection, the participants will be randomized to either an arthroscopic subacromial decompression (intervention group) or continuation of usual medical care (control group). The latter will be performed by a general practitioner according to the Dutch National Guidelines for Shoulder Problems. At inclusion, at randomization and three, six and 12 months post-randomization an outcome assessment will take place. The primary outcome measure is the patient-reported Shoulder Disability Questionnaire. The secondary outcome measures include both disease-specific and generic measures, and an economic evaluation. Treatment effects will be compared for all measurement points by using a GLM repeated measures analyses.

**Discussion:**

The rationale and design of an RCT comparing arthroscopic subacromial decompression with usual medical care for subacromial impingement syndrome are presented. The results of this study will improve insight into the best moment of referral for surgery for SIS.

## Background

Shoulder disorders are encountered frequently in general practice. In a Dutch study the cumulative incidence of shoulder problems was estimated to be 23.1/1000 patients/year [1]. For the neck and upper extremity it was the most commonly presented musculoskeletal complaint. A differentiation between various diagnoses of shoulder problems in general practice was presented in another Dutch study [2]. Subacromial impingement syndrome (SIS) was the most frequently recorded disorder (44%).

The primary treatment of SIS is conservative. In primary health care a broad spectrum of conservative treatments for SIS is available: rest, non-steroidal anti-inflammatory drugs (NSAIDs), corticosteroid injections, physiotherapy and manual therapy. In the Netherlands, the choice of treatments for shoulder conditions is proposed by the National Guidelines for Shoulder Problems, published by the Dutch College of General Practitioners [3]. If patients do not respond sufficiently to these nonoperative measures, referral to an orthopedic surgeon for evaluation for (arthroscopic) subacromial decompression is recommended [4]. The best moment of referral is not well defined though, so a therapeutic dilemma for the general practitioner exists: how many different treatments from the spectrum of nonoperative interventions should be repeated or tried out if previous ones have failed? And how long should one wait for recovery before referring? The preoperative duration of symptoms reported in different articles published in the last two decades on surgery for SIS is quite long, ranging from an average of 18 to 40 months [5-9]. Expert opinions advocate orthopedic referral is warranted for patients who do not respond to nonoperative measures after (three to) six months [10-13]. Moreover, several observational studies report a significantly better outcome of surgery in patients who had a short symptom duration compared to those who had prolonged symptoms before surgery [6,9]. From these studies it seems that the moment of referral is crucial. However, approximately 60% of the patients recover within 27 months with nonoperative measures, which has to be taken into consideration [14]. Early surgery would therefore not always be appropriate because patients could recover nonoperatively. On the other hand, late surgery might lead to smaller improvements of shoulder function. To improve insight, we designed an interdisciplinary treatment strategy called TRANSIT (TRANSmural treatment strategy for Subacromial ImpingemenT), which contains rules to treat patients with SIS in primary care and a well-defined moment of referral to an orthopedic surgeon for arthroscopic acromioplasty. The TRANSIT outline for the treatment of SIS will be tested in a randomized controlled trial (RCT), comparing treatment results of participants allocated to arthroscopic subacromial decompression with continuation of usual medical care by the general practitioner. The present paper reports on the content of TRANSIT and the methodological design of this RCT.

## Methods/Design

### Study design

The study is designed as a randomized controlled trial to evaluate the effectiveness of a new interdisciplinary treatment strategy for SIS. Figure 1 presents the design. The Medical Ethics Committee of University Medical Center Groningen has approved the study design, the protocols and the informed consent procedure. Participants are assigned at random to the control or to the intervention group. The follow up period after randomization is 12 months.

### TRANSIT: an interdisciplinary strategy

Initially, TRANSIT follows the National Guidelines for Shoulder Problems to diagnose and treat patients with SIS [3]. For all new patients, treatment starts with NSAIDs. If results following a maximum of two weeks of treatment are insufficient, therapy is continued with a subacromial corticosteroid injection. When ineffective, this injection is repeated within one month. In case of recurrence within 12 months after the first successful subacromial injection, eligible patients (see "selection of participants") are asked to participate in the study. Recurrence means patients having pain again, having increased pain or no longer experiencing pain relief. Included patients will receive another subacromial injection from their general practitioner, which if necessary can be repeated within one month. In case of a second recurrence within 12 months after the last successful injection, participants will be randomized to either an arthroscopic subacromial decompression performed within four weeks or continuation of treatment by the general practitioner according to the National Guidelines for Shoulder Problems. Participants who have a recurrence more than 12 months after the last injection will not be randomized. Patients who do not respond to two injections within one month will not be included either. Their long preoperative duration does not fit within the concept of this study, in which participants have surgery after an on average shorter-than-usual duration of symptoms.

For both NSAIDs and subacromial corticosteroid injections there is evidence of their effectiveness for SIS, albeit for the short term (up to a nine-month period) [15,16]. The reason for repeating a subacromial injection within a month in case of ineffectiveness is to target inaccuracy of subacromial injections. Several studies have reported on accuracy rates, ranging from 60 to 80% [17-20]. In addition to being a treatment, the subacromial injection constitutes a diagnosis itself (Neer impingement test) [13]. The injection fluid is a mixture of a corticosteroid and a local anesthetic (lidocaine). When a subacromial injection eliminates the pain immediately (as a result of the injected lidocaine), it confirms the diagnosis of SIS. If the injection does not eliminate the pain immediately, the diagnosis might be wrong or the injection could have been placed inaccurately. Furthermore, a positive reaction on a subacromial injection predicts better patient recovery following arthroscopic subacromial decompression compared to patients who have a negative reaction but a confirmed diagnosis through imaging [21].

### Setting

The trial is carried out in 50 general practices within an area of 20 kilometers from University Medical Center Groningen (UMCG) and at the Department of Orthopedic Surgery of UMCG. A total of 160 general practices in the surrounding area of Groningen were sent letters inviting them to participate in this study. Forty interested general practitioners attended an information meeting about the study protocol. Following a standard protocol, they were instructed in injecting into the subacromial space, which they subsequently practiced on phantoms and fresh-frozen cadaver shoulders. Another 10 general practitioners who could not attend the meeting were visited at their practice to be informed about the trial.

### Study population

#### Sample size

The aim is to include 70 participants in the study. This number is based on the assumption that one year after randomization 50% of the participants will have recovered with conservative treatment [22,23] and 85% will successfully recover by means of arthroscopic subacromial decompression. The latter assumption is based on recovery rates presented in earlier studies in which successful results of arthroscopic subacromial decompression are reported in 86 to 95% of the cases [24-26]. A power analysis has been based on the effects of these treatments on shoulder function. In this study shoulder function will be measured with the Shoulder Disability Questionnaire, which is an outcome measure comparable to the instruments used in the referred articles. In order to detect a clinically relevant difference in shoulder function (35% differences in means) one year after randomization between the intervention and control group, 64 participants are needed – 32 in each group. These numbers are based on a power (1-B) of 0.80 and a significance level of 5% (two-sided). When a dropout rate of 10% is taken into account, 70 participants are to be included.

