### Statistical analyses

To estimate the effect of the interventions, analyses will be performed using SPSS 12.0 for the outcome measures. The baseline characteristics from both study groups will be compared for equality by means of an Independent Samples T-test (p-value 0.05) for continuous variables and a chi-square test for dichotomous variables. To compare treatment effects from measurement points T_0 _to T_4_, a GLM repeated measures analyses will be performed. Data will be analyzed according to the intention-to-treat principle and the per-protocol principle.

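### The 32 per group rests on recovery proportions of 50% and 85% but is presented as 80% power for a difference in SDQ means, so the 80% is not established for the primary analysis

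*Protocol article*

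**What the plan says.** All the sizing information is in the protocol article, Study population, Sample size. The assumption is that at one year "50% of the participants will have recovered with conservative treatment [22,23] and 85% will successfully recover" after arthroscopic decompression. The section then says that the power analysis concerns shoulder function, to be measured with the SDQ, and that the SDQ is comparable to the instruments in the cited studies. The effect is given as "In order to detect a clinically relevant difference in shoulder function (35% differences in means) one year after randomization", and the result is "64 participants are needed – 32 in each group", at 80% power and a two-sided 5% level.

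Primary outcome measure makes the numeric SDQ score the primary outcome. Statistical analyses says that, to compare treatment effects from T0 to T4, "a GLM repeated measures analyses will be performed". Patient-perceived recovery, one item on a seven-point ordinal scale, is listed among the secondary outcomes.

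**The concern.** The 35% in the effect statement equals 85% minus 50%. That is a difference between two proportions of recovered patients, and calling it a difference in means turns it into a different quantity. A proportion recovered can be compared without an SD. A mean SDQ score cannot, and the section gives no SDQ mean, SD, standardised effect or recovery threshold that would connect the two.

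At stake is what the 80% refers to. A reader of a non-significant SDQ result would take it that the trial had an 80% chance of detecting the stated difference on that scale. The article does not support this, because the SDQ difference it could detect with 80% power is not given.

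**Working it through.** **Inputs from the article (Sample size):** recovery 0.50 and 0.85; power 0.80; two-sided 5%; 32 per group. **Assumed here, because the article gives neither:** SDQ SDs of 20, 25, 30 and 35 points, and a control mean of 50 points.

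**1. Reproducing the 32 as two proportions.** The pooled proportion is (0.50 + 0.85)/2 = 0.675.

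- Uncorrected: n = [1.960 × √(2 × 0.675 × 0.325) + 0.842 × √(0.50 × 0.50 + 0.85 × 0.15)]² / 0.35² = (1.298 + 0.517)² / 0.1225 = 26.9 per group. This does not give 32.
- Continuity-corrected: n/4 × [1 + √(1 + 4/(n × 0.35))]² = 26.9/4 × (1 + 1.194)² = 32.4 per group. Strict rounding up gives 33.
- Fisher's exact test, by enumeration: power 0.797 at 31 per group and 0.815 at 32, so 32 is the size at which it passes 80%.

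**2. Trying to reproduce the 32 as two means.** n = 2 × (1.960 + 0.842)² / d² = 15.70 / d². With d = 0.70 this is 32.04. If 35% is read as 35 SDQ points, d = 0.70 needs an SD of 35/0.70 = 50 points, which the article does not state. If the score runs from 0 to 100, that is about the largest SD possible.

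**3. What 32 per group gives on the SDQ.** A two-sample t-test at 12 months has 80% power for d = 0.711. Two readings of the 35% are shown: 35 points, and 35% of a control mean of 50 (0.35 × 50 = 17.5 points).

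| Assumed SD | Difference with 80% power (0.711 × SD) | Power for 35 points | Power for 17.5 points |
|---|---|---|---|
| 20 | 14.2 | >99% | 93% |
| 25 | 17.8 | >99% | 79% |
| 30 | 21.3 | >99% | 63% |
| 35 | 24.9 | 98% | 50% |

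These figures use one time point without adjustment. Adjusting for the pre-treatment SDQ multiplies the residual SD by √(1 − r²). With an assumed correlation r of 0.5 the factor is 0.866, and the 63% becomes about 76%.

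**The case against.** The article names no formula, so the two-proportion origin is an inference. The continuity-corrected value rounds up to 33, while a means calculation with d = 0.70 gives 32.04. This stands as a caution, and one can say only that no SDQ mean or SD is reported. But the section itself says that the number rests on the two recovery rates, and the means route needs an unstated SD of about 50. On either route the 80% is not shown for the SDQ.

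Sizing on proportions may also be conservative. Suppose recovery is a cut-off on a normally distributed function score with equal variances. Then 50% v 85% corresponds to d = 1.04, which needs about 16 per group, and 32 per group gives 98% power. This is a fair argument, but the article neither makes it nor defines recovery on the SDQ. Saying that the instruments are comparable may justify borrowing recovery rates; it does not supply an SD.

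Three stronger readings are tempting and are not supported:

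- **That the trial is underpowered.** The table shows power well above or below 80%, depending on an SD and a meaning of 35% that the article does not give.
- **That no analysis of recovery is planned.** Patient-perceived recovery is a listed outcome, and a condensed article may leave its handling to the full plan. What can be said is that the article describes no test of proportions.
- **That the arithmetic is wrong.** For two proportions it is sound.

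Finally, a non-significant SDQ result would be read mainly from its confidence interval, which this point leaves untouched. That limits the harm.

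**Conclusion.** The point holds as a mismatch of endpoint and effect size. The 32 per group agrees with a comparison of 50% and 85% recovered, and the effect is then mislabelled as a difference in SDQ means. The stated 80% is not established for the primary SDQ analysis. What 32 per group does support is 80% power for 0.71 SD at 12 months, or about 14, 18, 21 or 25 points at SDs of 20, 25, 30 or 35. Over those SDs, power is about 98% or more if 35% means 35 points, and 93% down to 50% if it means 17.5 points. The SDs and the control mean are assumptions, and the calculation is a simple t-test; adjustment for the pre-treatment score would raise the lower figures. The text should be corrected, but the design and the primary analysis need not change on this account.

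**What to change.** In Sample size:

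1. Delete the parenthesis that calls the effect a 35% difference in means.
2. State that 64 was sized on 50% v 85% recovered at one year, and name the test or formula used.
3. Add the power for the primary outcome: 32 evaluable participants per group give 80% power, two-sided 5%, for a 12-month SDQ difference of 0.71 SD. Show the points over a sourced or openly assumed SD range, for example 14, 18, 21 and 25 points at SDs of 20, 25, 30 and 35. If the difference is still called clinically relevant, justify that separately, because a value solved back from a fixed sample size shows only sensitivity.
4. If the 50% v 85% basis is kept, add a secondary analysis of the proportion recovered at 12 months, as a risk difference with 95% confidence interval. Define recovery in advance, either by an SDQ threshold or by a cut-point on the patient-perceived recovery item. The article gives neither, and does not say that the 50% and 85% were measured with that item.

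The cost is protocol or analysis-plan wording, a source or stated range for the SDQ SD, and at most one extra analysis of data already collected. No extra patients are needed.

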#### Selection of participants

Subjects participating in the study are recruited by the general practitioners involved. They introduce the study to patients who seem eligible and give interested patients a brochure about the trial, to be read at home. After having received consent, the general practitioners fax the name and telephone numbers of the interested patients to the research team. Subsequently the researcher calls the interested patients within one week. During this conversation the aim and implications of the study are explained again and the eligibility criteria are checked. Patients are eligible for participation when they meet the inclusion and exclusion criteria presented in Table 1.

If patients meet these criteria and wish to join the study, an informed consent form is signed before participation begins. The new participants receive another subacromial corticosteroid injection from the general practitioner for treatment of their first recurrence. If ineffective, this injection will be repeated within one month. Participants who have a recurrence of problems within one year after the last injection will contact their general practitioner, who will inform the researcher by fax. Subsequently the participant will be invited to visit the researcher at UMCG for a physical outcome measurement and to be randomized to one of the two treatment groups. Participants who do not have a recurrence within one year will not be randomized.

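### The target of 70 is stated as participants included, but the 64 behind the 80% power must be randomized, and no allowance is made for included participants who never reach randomization

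*Protocol article*

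**What the plan says.** The Sample size section assumes that "one year after randomization 50% of the participants will have recovered with conservative treatment" and that "85% will successfully recover by means of arthroscopic subacromial decompression". From these rates, also described there as a 35% difference in means, it arrives at 64 participants, 32 per group. On the error rates it says "These numbers are based on a power (1-B) of 0.80" and "a significance level of 5% (two-sided)". It ends: "When a dropout rate of 10% is taken into account, 70 participants are to be included". The section also opens by giving 70 as the number it aims to include.

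Elsewhere the article treats inclusion and randomization as two events:

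- The abstract (Methods/Design) places inclusion at the first recurrence, before the study injection: "After inclusion they will receive injection treatment again by their general practitioner".
- Outcome assessment gives them separate time points, T0 for inclusion and T1 for randomization.
- Selection of participants says: "Participants who do not have a recurrence within one year will not be randomized".
- The section on the TRANSIT strategy adds: "Participants who have a recurrence more than 12 months after the last injection will not be randomized".

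The article gives neither the proportion of included participants expected to have a timely second recurrence nor a number to be randomized.

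**The concern.** The 64 and the 70 count people at different stages. The 64 are needed in the two randomized arms at one year. The 70 are, in the article's own terms, people who have entered at T0. Between T0 and T1 the design removes everyone whose shoulder does not recur within a year of the study injection. That removal is planned and is separate from dropout. The article itself credits such injections with a short-term effect of up to nine months, so near-universal recurrence cannot be taken for granted.

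If 70 inclusions were used as the recruitment target, the randomized comparison would be smaller than the one that was powered. The trial is meant to inform referral guidelines, so a real benefit could be missed, or the confidence interval could be too wide to settle the question.

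**Working it through.** **Inputs from the Sample size section.** Recovery 0.50 v 0.85, two-sided alpha 0.05 (z = 1.960), power 0.80 (z = 0.842), 32 per arm, 10% dropout, target 70.

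**Input not in the article.** The second-recurrence rate r, meaning the share of included participants who reach randomization. It is an assumption and is shown as a range.

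**Step 1: reproduce the 64.** The article does not name its formula, so three were tried.

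- Two proportions, no continuity correction: n = [1.960·√(2·0.675·0.325) + 0.842·√(0.50·0.50 + 0.85·0.15)]² / 0.35² = 26.9, so 27 per arm (54 in total).
- Two proportions, continuity-corrected: (26.9/4)·[1 + √(1 + 4/(26.9·0.35))]² = 32.4, so 33 per arm. At 32 per arm its power is 79.4%.
- Two means, difference 0.35 and SD 0.5 (the SD is assumed, since none is stated): n = 2·(0.5/0.35)²·(1.960 + 0.842)² = 32.04, in effect the stated 32 per arm.

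The second and third come close to 32. The first does not, but it is kept as the most favourable case.

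**Step 2: reproduce the 70.** 64 × 1.1 = 70.4, which is 70 after rounding down. The figure makes sense as a number to randomize. It has no second factor for the step from T0 to T1.

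**Step 3: follow 70 inclusions to the analysis.** Analysed = 70 × r × 0.9.

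- If everyone recurs in time (r = 1): 70 × 0.9 = 63.
- If nobody drops out: 64/70 = 91.4% must recur to reach 64.

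**Step 4: power over the assumed range of r.** Per arm n = 70 × r × 0.9 / 2, without rounding.

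| r | Randomized | Analysed | Per arm | Continuity-corrected | Means, SD 0.5 | Uncorrected |
|---|---|---|---|---|---|---|
| 1.0 | 70 | 63.0 | 31.5 | 79% | 79% | 86% |
| 0.9 | 63 | 56.7 | 28.4 | 73% | 75% | 82% |
| 0.8 | 56 | 50.4 | 25.2 | 66% | 70% | 77% |
| 0.7 | 49 | 44.1 | 22.1 | 59% | 64% | 71% |
| 0.6 | 42 | 37.8 | 18.9 | 50% | 58% | 64% |
| 0.5 | 35 | 31.5 | 15.8 | 40% | 50% | 56% |

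Rounding the last row up to 16 per arm moves the uncorrected figure to 57% and changes nothing of substance.

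**Step 5: inclusions needed to randomize 70.** 70/r gives 78 at r = 0.9, 88 at 0.8, 100 at 0.7, 117 at 0.6 and 140 at 0.5.

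**The case against.** The best defence is that the authors meant 70 randomized. Everything around the figure concerns the randomized comparison: recovery one year after randomization, two groups, 32 in each. The arithmetic 64 × 1.1 fits that reading. The TRANSIT section also uses the word included loosely once, about patients who do not respond to two injections. On this reading power is about 79 to 80%, and what is wrong is the label and the absence of an inclusion figure. This objection stands as a plausible account of the intent. It does not rescue the text, because the abstract, the TRANSIT section and the T0/T1 schedule all put inclusion before randomization. The correction is the same either way.

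It could also be said that the 10% covers every loss after inclusion. Then non-recurrence, late recurrence and loss during a year of follow-up would together have to stay within 6 of 70 (8.6%) to leave 64. The article offers nothing to support that.

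The size of the shortfall is indeed unknown. At r = 0.9 it is modest, and the uncorrected formula still gives 82%. That formula needs 54 analysed and keeps 80% power down to about r = 54/63 = 0.86, but it does not produce the stated 64.

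A reader might go further and infer four things that the article does not support:

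- **Recruitment will close at 70 inclusions.** The article gives an aim and no closing rule.
- **The analysed number will be far below 64.** That depends on a recurrence rate which is not given.
- **Non-responders to the study injection are a further loss after inclusion.** This rests on the one loosely worded sentence about non-response, which may describe patients who never entered.
- **A null result could not be interpreted.** Lower power widens the interval, but an estimate with its interval can still be read.

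**Conclusion.** The point holds as a mismatch between the stated target and the design. Read in the article's own terms, 70 inclusions do not support 80% power for a comparison that needs 64 after randomization. With the stated 10% dropout, 63 is the ceiling. That shortfall of one is immaterial in itself, and the loss that matters is non-recurrence, for which nothing is allowed. The direction is certain and the amount is not: about 73 to 82% power at an assumed recurrence rate of 0.9, 66 to 77% at 0.8 and 40 to 56% at 0.5. These figures rest on the article's 50% v 85%, its 10% dropout, equal arms, and (for the means version) an assumed SD of 0.5. The finding is that the target is wrong as written. It does not show that the trial was in fact underpowered.

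**What to change.** Restate the sample size as a randomized number: 64 evaluable, and about 70 randomized to allow for 10% loss after randomization. Then give the expected number of inclusions as 70 divided by an explicitly assumed second-recurrence rate, with the basis for that rate, and say that recruitment closes when the randomized count is reached. If 70 inclusions is the practical limit, keep it, state how many are expected to be randomized, and restate the power for that number.

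If 70 randomized was always intended, the cost is a change of wording and one added figure. If 70 inclusions was intended, the cost is either a larger recruitment target (88 at an assumed rate of 0.8, 140 at 0.5) or a lower stated power. The treatments, outcome measures and analysis are unaffected.
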